#### Qualitative assessment

To help us open the “black box” of HIVRR+MF delivery, we conduct semi-structured, in-depth interviews at three points in time during study implementation: at 1 month, 3 months and 15 months post randomization and session 1 (corresponding to the end of the financial literacy sessions, vocational trainings sessions for HIVRR+MF participants, and to the month-15 follow-up assessment for all participants). We randomly select one participant from each cohort (approximately 50 women) to complete interviews. Questions focus on participants’ perception of the intervention, their experience with both the HIV-risk reduction and microfinance components and their reaction to the various role-plays, activities and goal-setting assignments, as well as the reactions or interactions with family, friends, colleagues related to their participation, factors promoting the use of the session information and skills and barriers impeding participation. Importantly, questions also focus on perceptions of how the intervention influenced participant safety, including any policy involvement, stigma or discrimination, drug use before and during the intervention, and savings and the potential access to matched savings, and alternative income sources. All interviews are audio-taped, transcribed and translated to English.

Cost-effectiveness is measured through a series of staff questionnaires, asking project staff about the time they spend on various intervention activities, along with budgets and financial records.

### Data analysis

In assessing primary outcomes (STI, HIV, and HCV incidence, unprotected sexual acts and unsafe injection acts), our over-arching modeling approach estimates intervention differences (HIVRR alone versus HIVRR+MF) longitudinally using a generalized estimating equations (GEE) approach, a flexible extension of conventional regression models, to account for repeated measures and clustering imposed by randomizing individuals in groups of six to eight women per cohort. STIs will be summarized as both a count (number of positive test results for any of the five STIs of interest (syphilis, gonorrhea, chlamydia, trichomoniasis, mycoplasma)) over the entire follow-up period, as well as a binary indicator of a positive test for any STI of interest at each follow-up time. The primary analysis will be a logistic GEE (e.g., presence/absence of an incident STI post randomization), accounting for clustering imposed by the study design in having women receiving their randomized intervention in cohorts of six to eight women each. Additionally, secondary analyses will consider intervention effects on HIV and HCV incidence as operationalized by binary indicators of testing positive for either, respectively, over the entire follow-up. We will employ logistic (binary outcomes) and Poisson (count outcomes) GEE models to estimate intervention effects as appropriate. We will implement an intent-to-treat approach for all analyses. Model estimates will be presented as estimates of incidence risk ratios or odds ratios, as appropriate, and corresponding 95% confidence intervals (CIs) and *p* values will be calculated for inference. Additionally, a logistic GEE modeling approach will be implemented for dichotomous outcomes (e.g., GEE with specified logit link) when evaluating the following outcomes: (1) self-reported unprotected vaginal and anal sexual acts with both regular and paying partners and (2) self-reported unsafe injection acts. Again, we will be interested in estimate rate ratios or odds ratios comparing HIVRR+MF to HIVRR alone. A Poisson GEE modeling strategy (e.g., GEE with specified log link) will be implemented to evaluate remaining secondary outcomes (1) self-reported number of unprotected vaginal and anal sexual acts with both regular and paying partners and (2) self-reported number of unsafe injection acts. To evaluate the secondary aims of the study related to potential moderating effects, we will expand these models to include “moderator X intervention” interaction terms along with the corresponding main effects and will assess examine the significance of each moderator on intervention effects through these interaction terms.

To examine whether key, theory-driven variables mediate the intervention’s effects on the primary outcomes, again we expand the logistic GEE modeling framework from the primary aim to examine (1) whether the HIVRR+MF improves the primary outcome compared to HIVRR alone; (2) whether the intervention improves each mediator; and (3) whether improvements in the mediator over time are associated with improvements in the primary outcome over time.

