## Methods/design

This study uses a cluster randomized controlled trial (c-RCT) to evaluate a combination HIVRR and microfinance (MF) intervention among FSW who use drugs in Kazakhstan. The study compares two arms: a combination HIVRR+MF intervention treatment arm and a control arm, which receives the HIVRR component alone. The study assesses outcomes over a 15-month period, which encompasses up to 3 months of intervention activities, and 12 months of follow-up. Study recruitment and enrollment began in May 2015, and follow-up data collection will be completed in October 2018.

The theoretical framework for the study is shown in Fig. 1. The primary aim of the study is to test whether participants assigned to the combined HIVRR+MF condition have improved outcomes on a number of indicators, as compared to those assigned to the HIVRR condition. These indicators include: (1) a lower cumulative incidence of biologically confirmed STIs (syphilis, gonorrhea, trichomoniasis, chlamydia and mycoplasma), (2) a lower rate of new HIV and hepatitis C virus (HCV) cases, (3) a greater decrease in the number of unprotected vaginal and anal sexual acts and a greater increase in the proportion of protected sexual acts with both regular and paying partners, (4) a reduction in the proportion of unsafe injection acts for those participants who inject drugs, and (5) a lower proportion of monthly income from sex work. These outcomes are summarized in Table 1.

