#### Power and sample size

Power and sample size considerations for this proposal prioritized sufficiently powering the study to detect intervention effects on incidence for the following biological outcomes: STIs (syphilis, gonorrhea, trichomoniasis, chlamydia, and mycoplasma), HIV and hepatitis C virus (HCV). Using baseline prevalence estimates from our prior work in similar populations (e.g., 10%, 28%, and 75%, for STIs, HIV, and HCV, respectively) [29], we conservatively focused on the least prevalent of the three biological outcomes of interest, STIs. We noted that if we were sufficiently powered to estimate intervention efficacy for the least prevalent outcomes, we would also be sufficiently powered to detect intervention effects for the others. Using these prevalence estimates, we determined a range of plausible incidences based on our experience in similar settings. We first calculated crude (unadjusted for clustering by cohort) using a conventional approach to detect differences in a binary outcome (e.g., incidence) in two groups assuming an *α*-level of 0.05 for a two-sided hypothesis test of an overall intervention effect. Crude sample size estimates were then inflated by the “variance inflation factor” as described in Donner and Klar [30], to account for the likely correlation of outcomes induced by the study’s cluster randomized design. Finally, we adjusted 20% attrition over the 15-month follow-up. We considered scenarios of modest (intraclass clustering coefficient (ICC) equal to 0.005) and moderate (ICC = 0.01) clustering effects. In summary, we determined that randomizing 350 women in equal proportions to each intervention (175 to HIVRR and HIVRR+MF) would ensure that 80% power to detect true relative risks of 0.25 and ICC = 0.01. This attrition and clustering adjusted sample size corresponds to detecting STI incidence relative risks (RR) equal to 0.25 comparing women randomized to HIVRR+MF to HIVRR alone, where the assumed STI incidence over the study follow-up period is 0.043 and 0.144, respectively. In these calculations, the assumed incidence in HIVRR alone of 0.144 represents a decrease of approximately 40% from the estimated baseline prevalence of 28% from our prior work in this population [29]. Because the other biological outcomes of interest are more prevalent, we expect to have greater than 80% power to detect similar intervention effects.

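### The article contradicts itself on which outcomes are primary; incident STI should be named the single primary outcome, as the stated primary analysis and the sample size already imply

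*Protocol article*

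**What the plan says.** All places are in the protocol article.

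- **Methods/design, primary aim.** The aim is to test whether women in the combined arm "have improved outcomes on a number of indicators, as compared to those assigned to the HIVRR condition". Five numbered indicators follow: STI incidence; new HIV and HCV cases; number of unprotected acts and proportion of protected acts; unsafe injection; share of income from sex work.
- **Data analysis, opening.** "In assessing primary outcomes (STI, HIV, and HCV incidence, unprotected sexual acts and unsafe injection acts". Income is not in this list.
- **Data analysis, a few sentences on.** "The primary analysis will be a logistic GEE (e.g., presence/absence of an incident STI post randomization".
- **Data analysis, next.** "secondary analyses will consider intervention effects on HIV and HCV incidence as operationalized by binary indicators".
- **Data analysis, later.** "A Poisson GEE modeling strategy (e.g., GEE with specified log link) will be implemented to evaluate remaining secondary outcomes". The outcomes meant are the self-reported numbers of unprotected acts and of unsafe injections.
- **Data analysis, mediation.** The sentence begins with primary outcomes in the plural, then asks "whether the HIVRR+MF improves the primary outcome compared to HIVRR alone", in the singular.
- **Power and sample size.** The 0.05 level is given once, "for a two-sided hypothesis test of an overall intervention effect", and the worked scenario is STI incidence.

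**The concern.** Choosing the primary outcome is a protocol-level decision. This article makes the choice and then contradicts it. HIV and HCV incidence are both primary and secondary. The number of unprotected acts belongs to the primary aim and is also called secondary. Income belongs to the primary aim but not to the list of primary outcomes.

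What is at stake is the standing of the trial's main claim. A report that treats HIV incidence or unprotected acts as primary could cite this text, and so could a report that treats them as secondary. The sample size spends the whole 5% on one comparison. If several outcomes could each support a primary claim, that 5% would no longer describe the risk of a false one.

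**Working it through.** **1. Labels side by side**

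| Outcome | Primary aim (Methods/design) | Opening list (Data analysis) | Later text (Data analysis) |
|---|---|---|---|
| Incident STI | yes | primary | the example given for the primary analysis |
| HIV incidence | yes | primary | secondary |
| HCV incidence | yes | primary | secondary |
| Unprotected acts | yes | primary | number: secondary; dichotomous form: no label |
| Unsafe injection | yes | primary | number: secondary; dichotomous form: no label |
| Income from sex work | yes | not listed | not mentioned |

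Only incident STI keeps the same status throughout.

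**2. What the 350 was sized for**

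Inputs from Power and sample size: STI incidence 0.144 (HIVRR) and 0.043 (HIVRR+MF), two-sided 0.05, power 80%, ICC 0.01, attrition 20%. Cohorts hold six to eight women (Group assignment and randomization); 7 is used here.

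- Pooled two-proportion formula: n = [1.96·√(2·0.0935·0.9065) + 0.8416·√(0.144·0.856 + 0.043·0.957)]² / 0.101² = 129.2, so 130 per arm.
- Design effect: 1 + (7 − 1)·0.01 = 1.06.
- After attrition: 130·1.06/0.8 = 172.3, so 173 per arm and 346 in total. Cohorts of 6 and 8 give 342 and 348.

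The planned 350 is therefore reproduced within 3% from one STI test at the full 0.05. Power with 140 evaluable women per arm is about 81%. The two stated rates were used because they reproduce 350. Their ratio is 0.043/0.144 = 0.30; the stated relative risk of 0.25 would give about 292.

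**3. Error rate under each reading**

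- *STI is the sole primary outcome:* 5%, or 2.5% for a false claim of benefit.
- *Any of the five listed outcomes counts as success at 0.05:* if independent, 1 − 0.95⁵ = 22.6%, and for benefit only 1 − 0.975⁵ = 11.9%.

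The documents give no correlations between the outcomes. Simulation of five equally correlated two-sided z-tests (1,000,000 draws) at assumed values of 0.5 and 0.9, beside the independent case, gives:

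| Correlation | At least one false positive | False claim of benefit |
|---|---|---|
| 0 | 22.6% | 11.9% |
| 0.5 (assumed) | 18.3% | 9.1% |
| 0.9 (assumed) | 10.1% | 5.1% |

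**4. Cost of keeping five primary outcomes with success on any one**

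Bonferroni gives 0.05/5 = 0.01 per test. The STI comparison then needs 193 per arm before inflation, and 193·1.06/0.8 = 255.7, so 256 per arm and 512 in total. With 350 randomized, its power falls from about 81% to about 60%.

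**The case against.** The strongest reply is that the text already points to one primary outcome. It names a single primary analysis with incident STI as the case, the mediation text ends in the singular, the sample size rests on STI, and the later labels move other outcomes down. On that reading the error rate is 5%. This is the most sensible reading, and it stands as evidence of intent. The text does not secure it, though. STI enters the primary-analysis sentence only as an example, in a paragraph that has just listed five primary outcomes, and the primary aim adds income.

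A reader might infer that five outcomes are each tested at 0.05 as separate routes to success, so that the planned error rate is already well above 5%. The documents do not say this. The 0.05 level appears only in the sample-size section. The Data analysis section promises 95% intervals and p values but states no such success rule.

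A reader might also treat the lack of a multiplicity procedure as a fault in itself. An article commonly leaves that to the SAP, which is not shown, so it is not counted here. Two further inferences also lack support. Nothing in the text shows that labels will be chosen after the results are seen. And the power section does not ignore HIV and HCV: it expects more than 80% power for them.

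**Conclusion.** The concern holds as a contradiction in the outcome hierarchy, visible within the article and independent of any unseen SAP. It does not hold as a statement that the planned type I error exceeds 5%.

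The size depends on how the contradiction is resolved. If STI alone is primary, there is no inflation. If any of the five listed outcomes may carry the claim at an unadjusted 0.05, the chance of a false positive is about 10% to 23%, and of a false claim of benefit about 5% to 12%. Those ranges assume no true effect on any outcome and equal pairwise correlations from 0 to 0.9. Because the sample size uses the full 0.05 for STI, the second reading cannot be repaired by splitting alpha without more women or less power.

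**What to change.** Before the final analysis, state that incident STI, analysed by the logistic GEE already described, is the single primary outcome, and remove the wording that makes it only an example. Label HIV incidence, HCV incidence, unprotected acts, unsafe injection and income from sex work as secondary, in the same terms, in the primary aim, the Data analysis section (including the mediation paragraph) and the power section. Multiplicity handling among the secondary outcomes can be left to the SAP.

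The cost is wording only: N stays at 350 and the primary claim stays at 5%. Follow-up was due to run to October 2018, so the article leaves time for this. The downside is that a positive behavioural, HIV or HCV result could not be the trial's headline claim.

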#### Assessments

Baseline and follow-up assessments are administered by research assistants in project field office locations. Assessments take place at a pre-intervention baseline (prior to cohort assignment and randomization), then at 6, 9, and 15 months after randomization and intervention session 1 (which occur simultaneously, as participants are randomized as a cohort immediately prior to beginning the first intervention session). Since the HIVRR+MF treatment arm receives an intervention that is approximately 2.5 months longer than the control arm, we allocated an additional 2.5 months of follow-up time for in the control arm. Behavioral questionnaires are utilized at all assessments, and biological testing procedures are conducted at baseline, month-9 and month-15 assessments.

Behavioral questionnaires are conducted using computer-assisted self-interviewing (CASI) methods, with the same survey tool that the research assistants use to assess study eligibility and which can be completed in approximately 2 h. The baseline behavioral questionnaire addresses the main outcome variables of interest to the study (number of partners, number of sex acts, number of sex acts which are unprotected, number of paying partners, incidences of drug use, incidences of injection drug use and incidences of risky injection behaviors) in addition to several of the theoretical constructs underlying the study (self-efficacy in a number of risk-reduction behaviors, outcome expectancies and risk-reduction intentions) and a number of potential moderators (demographics, financial status, experience of IPV and gender-based violence (GBV), social support, linkage to care and service utilization). Table 1 contains a list of the specific measures used for each construct.

Follow-up assessments occur as early as 1 week before the exact follow-up date, and as late as 3 weeks after the exact follow-up date. Like the baseline behavioral questionnaire, the follow-up behavioral questionnaires address the main outcome variables, moderators and mediators of interest to the study. The follow-up questionnaires also include additional questions to assess how HIVRR+MF participants have utilized the vocational training and financial literacy training that they have received.

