To complement self-reports and utilize an objective assessment measure of risk behavior, we use biological assays to confirm HIV and STI status. We selected five STIs: syphilis, gonorrhea, chlamydia, trichomoniasis and mycoplasma as objective proxies of sexual risk behavior. The choice of these STIs was based on their high prevalence and incidence in this population and the availability of definitive treatment with a single-dose medication (which obviates STI medication treatment adherence and compliance issues). We also selected HCV to index drug-related risk behaviors. A clinical coordinator conducts biological testing in each project field office location. A complete description of test systems used is provided in Table 2.

**Table 2 Tab2:** Biotesting systems used

Infection	Testing specimen	Test system used	Sensitivity (95% CI^a^)	Specificity (95% CI^a^)
HIV	Finger stick (whole blood sample)	Alere Determine™ HIV-1/2 Ag/Ab Combo rapid test system [47]	99.9% (99.4–100.0%)	99.8% (99.5–99.9%)
Hepatitis C (HCV)	Dried blood spot	Murex anti-HCV (version 4.0) [48]	100% (94.79-100%)	99.88% (99.77–99.94%)
Syphilis	Dried blood spot	Murex ICE Syphilis [49]	100% (99.1–100%)	100% (99.2–100%)
Gonorrhea	Vaginal specimen	AmpliSense *N. gonorrhea*/*C. trahomatis*/*M. genitalium*/*T. vaginalis*-MULTIPRIME-FRT PCR [50]	N/A^b^	N/A^b^
Trichomoniasis	Vaginal specimen	AmpliSense *N. gonorrhea*/*C. trahomatis*/*M*. *genitalium*/*T. vaginalis*-MULTIPRIME-FRT PCR [50]	N/A^b^	N/A^b^
Chlamydia	Vaginal specimen	AmpliSense *N. gonorrhea*/*C. trahomatis*/*M. genitalium*/*T. vaginalis*-MULTIPRIME-FRT PCR [50]	100% (73.3–100%)	100% (98.1–- 100%)
*Mycoplasma genitalium*	Vaginal specimen	AmpliSense *N. gonorrhea*/*C. trahomatis*/*M. genitalium*/*T. vaginalis*-MULTIPRIME-FRT PCR [50]	76.5% (50.1–93.0%)	100% (98.1–100%)

^a^CI confidence interval

^b^N/A estimates are not available for vaginal specimen samples

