Participants who test positive for any STI are provided with referrals and treatment. The clinical coordinator works with individual participants to ensure that they complete their course of treatment prior to randomization and session 1, ensuring that any STI acquired post randomization is an incidence STI, and, as soon as possible at follow-up, biotesting assessments. STIs acquired and treated between the baseline and month-9 assessment or between the month-9 and month-15 assessment at an external clinic are only included as an endpoint if it is self-reported by participants on their month-9 and month-15 assessments. The clinical coordinator refers participants who screen positive for syphilis to the local Skin and Venereal Disease Dispensary to receive additional confirmatory testing for syphilis, consultations with a physician, and treatment for active forms of syphilis. Treatment for HCV is not widely available in Kazakhstan, and clinical coordinators refer participants who test positive for HCV to specialized clinics for additional examination, monitoring, and treatment. Treatment for HIV is also limited in Kazakhstan. If participants receive a positive rapid test for HIV, the clinical coordinator refers them to the local AIDS center for confirmatory testing and treatment. HIV-positive participants sign an additional waiver allowing our study access to treatment records at the local HIV clinic. Clinical coordinators collect information on confirmatory testing (for newly diagnosed cases of HIV), viral-load test results, CD4 test results, and antiretroviral (ARV) medication history at every assessment period for each participant.

Participants receive the equivalent of US$10 for the baseline assessment, US$9 for the month-6 follow-up assessment, US$11 for the month-9 follow-up assessment, and US$16 for the month-15 follow-up assessment. The total possible reimbursements for assessments is US$46.

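### STIs are scored as positive tests, so one syphilis infection acquired before month 9 can be scored again at month 15

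*Protocol article*

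**What the plan says.** All references are to the protocol article.

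- **Aim (Methods/design).** The first listed indicator is "a lower cumulative incidence of biologically confirmed STIs".
- **Derived variables (Data analysis).** STIs are summarized as a count over the whole follow-up, the "number of positive test results for any of the five STIs of interest", "as well as a binary indicator of a positive test for any STI of interest at each follow-up time".
- **Models (Data analysis).** The plan states: "The primary analysis will be a logistic GEE (e.g., presence/absence of an incident STI post randomization". It adds: "We will employ logistic (binary outcomes) and Poisson (count outcomes) GEE models to estimate intervention effects as appropriate". The overall approach is longitudinal, with repeated measures and cohort clustering handled by GEE.
- **Timing (Assessments).** The plan says that "biological testing procedures are conducted at baseline, month-9 and month-15 assessments", so each STI is tested twice after randomization.
- **Tests (Assessments, Table 2).** Syphilis is tested on a dried blood spot. Gonorrhea, chlamydia, trichomoniasis and *Mycoplasma genitalium* are tested by PCR on a vaginal specimen.
- **After a positive result (Assessments).** Women with an STI are treated before randomization and as soon as possible at follow-up. Those who screen positive for syphilis are referred "to receive additional confirmatory testing for syphilis, consultations with a physician, and treatment for active forms of syphilis".
- **Contrast with HIV and HCV (Data analysis).** Each of these is a single yes/no indicator for the entire follow-up, so a woman can score only once for each.

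**The concern.** The aim is about new infections, while both derived variables are about positive results. The two agree only if an infection found and treated at month 9 tests negative by month 15 unless the woman is reinfected. The plan relies on treatment to secure this. That logic suits the four PCR-tested infections. It is less secure for a blood-based syphilis screen, because the plan itself sends screen-positives for confirmation and treats only active forms. It therefore accepts that a screen can be positive without active disease.

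Three things are at stake:

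- The count can exceed the number of infections.
- A month-9 syphilis infection can reappear as a month-15 event in the visit-level indicator. If the primary logistic GEE uses that indicator as written, the repeat enters the primary analysis too.
- Syphilis acquired before month 9 can weigh twice as much as syphilis acquired later. That early period includes the three months in which the microfinance components are still being delivered.

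**Working it through.** **1. The plan's own figure.** The plan gives no figure for the STI count. Its sample size rests on a binary incidence of 0.144 versus 0.043, two-sided α 0.05, power 80%, ICC 0.01, cohorts of 6 to 8 and 20% attrition (Power and sample size; Group assignment and randomization).

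With the pooled-variance formula and no continuity correction, n per arm = [1.96 × √(2 × 0.0935 × 0.9065) + 0.842 × √(0.144 × 0.856 + 0.043 × 0.957)]² / 0.101² ≈ 129.2, rounded up to 130. Multiplying by 1 + (m − 1) × 0.01, dividing by 0.80, rounding up and doubling gives 342 (m = 6), 346 (m = 7) and 348 (m = 8). This reproduces 350 to within 3%. No count enters the calculation, so the scoring rule does not affect it.

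**2. Two women under the literal rule.** Both are syphilis-negative at baseline, have one infection each and have no other STI.

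| | Month 9 | Month 15 | Count | True infections |
|---|---|---|---|---|
| A: infected in month 4, treated after month 9, screen still positive | 1 | 1 | 2 | 1 |
| B: infected in month 12 | 0 | 1 | 1 | 1 |

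Excluding or treating women who are positive at baseline does not change this, because A was negative at baseline.

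**3. Inflation of the count.** Three inputs are assumptions, because the documents do not give them:

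- s, the syphilis share of all incident STIs
- f, the share of infections acquired before month 9, set at 9/15 = 0.60 (constant incidence over 15 months)
- q, the probability that the screen is still positive at month 15

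With full retention, positives per infection = 1 + s × f × q.

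| s | q = 1 | q = 0.5 | q = 0 |
|---|---|---|---|
| 0.10 | 1.06 | 1.03 | 1.00 |
| 0.25 | 1.15 | 1.075 | 1.00 |
| 0.50 | 1.30 | 1.15 | 1.00 |

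For syphilis alone with q = 1, the figure is 0.6 × 2 + 0.4 × 1 = 1.6.

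**4. Month-15 indicator.** Under the same assumptions with q = 1, 9 of every 15 syphilis positives at month 15 (60%) among women negative at baseline would be carried over from month 9.

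**5. Effect on the ratio between arms (q = 1).** Let the control arm have 9 units of infection before month 9 and 6 after.

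- *Constant rate ratio of 0.30.* Both arms are inflated alike, and the ratio stays at 0.30.
- *No effect in months 0–3, then 0.30.* The intervention arm has 3 + 0.3 × 6 = 4.8 before month 9 and 0.3 × 6 = 1.8 after. The true ratio is 6.6/15 = 0.44. Positives give (4.8(1 + s) + 1.8)/(9(1 + s) + 6): 7.08/15.9 = 0.445 (s = 0.10), 7.8/17.25 = 0.452 (s = 0.25) and 9/19.5 = 0.462 (s = 0.50). For syphilis alone it is 11.4/24 = 0.475.
- *No effect until month 9, then 0.30.* The true ratio is 0.6 × 1 + 0.4 × 0.3 = 0.72. Positives give (0.6(1 + s) + 0.12)/(0.6(1 + s) + 0.4): 0.736, 0.757 and 0.785 for the same three shares.

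The ratio moves toward the early-period effect, and only when the early and late effects differ.

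**The case against.** The strongest reply is that the plan already fixes incidence as its target. The primary analysis is worded around an incident STI, and treatment before randomization is meant to make later infections incident ones. If the primary outcome is scored once per woman over follow-up, A and B both score 1 and there is no double weight. On this view, how to handle a repeat seropositive is a derivation detail for the statistical analysis plan, which is not shown. Part of this stands: the count is an additional summary, and the primary analysis is exposed only if the visit-level indicator is used literally. But the article does not leave the rule open. It states one, in terms of positive tests, and that rule does not match the aim.

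The second reply is that nothing in the documents says this syphilis screen stays positive after treatment. That is correct. The referral for confirmatory testing fits persistence but does not establish it, and with q = 0 the inflation disappears. The point is therefore that a woman can be counted twice, not that she will be.

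A reader might also infer two stronger claims that the documents do not support:

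- **Early infections of every kind get double weight.** The other four STIs are tested by PCR and treated, so a month-15 positive is intended to be a new infection.
- **The cost-effectiveness results are inflated.** The Cost-effectiveness analyses section builds averted transmissions from a Bernoulli model of risk behavior, not from a tally of positive tests.

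**Conclusion.** The point holds for syphilis only. The stated count and visit-level indicator record positive tests, the aim is new infections, and nothing in the article prevents one syphilis infection from scoring at both month 9 and month 15.

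The size is modest and conditional. With a screen that always stays positive, full retention and constant incidence, the five-STI count is too high by 6%, 15% or 30% for assumed syphilis shares of 10%, 25% or 50%. It is too high by less if some tests revert. A constant treatment effect leaves the ratio unbiased. In the time-varying examples above, the composite ratio moves from 0.44 to at most 0.462, or from 0.72 to at most 0.785, for shares up to 50%.

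It would go too far to conclude that the primary analysis is wrong, since its wording points to incident infection. What is missing is agreement between that wording and the variables defined beside it.

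**What to change.** Add one derivation rule that applies to both the count and the visit-level indicator. Score syphilis only at the first change from negative to positive after baseline, and do not score a repeat positive at month 15 as a new event unless reinfection is documented. Leave the other four STIs as they are, so a woman with a month-9 syphilis event can still score for any of them at month 15. State that the primary logistic GEE uses the indicator derived in this way.

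The rule needs no new samples and does not change the sample size. Its cost is that some true syphilis reinfections between months 9 and 15 may be missed. The report should say so, since women enter this trial on the basis of recent sex trading and unprotected sex. Reporting how many women were syphilis-positive at both follow-up visits would show how much the rule matters.
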